**Methods:**

An assessor-blinded, pragmatic, single-centre randomized controlled trial will be performed. Adults (*n* = 150) mechanically ventilated for < 48 h from four ICUs who are estimated to need > 7 days of critical care will be randomized (1:1) to receive either standard of care or FES-CE-based intensified rehabilitation, which will continue until ICU discharge. Primary outcome: quality of life measured by 36-Item Short Form Health Survey score at 6 months. Secondary outcomes: functional performance at ICU discharge, muscle mass (vastus ultrasound, N-balance) and function (Medical Research Council score, insulin sensitivity). In a subgroup (*n* = 30) we will assess insulin sensitivity and perform skeletal muscle biopsies to look at mitochondrial function, fibre typing and regulatory protein expression.

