Secondly, *mitochondrial dysfunction* in skeletal muscle may play a role in the development of ICUAW. Mitochondrial depletion and dysfunction of mitochondrial respiratory complexes I and IV has been demonstrated in acute severe sepsis in association with multiorgan failure and death [52], and early activation of mitochondrial biogenesis predicted survival [53]. Our group has recently demonstrated in two pilot studies [54, 55] that, compared to healthy controls, there is a 50% reduction of mitochondrial functional capacity in skeletal muscle in the patients with protracted critical illness and ICUAW. This is accompanied by a significant relative increase in the abundance and functional capacity of respiratory complex II, which delivers electrons to the respiratory chain from fatty acid oxidation [54]. Weber-Carstens et al. [48] demonstrated that insulin fails to activate GLUT-4 translocation to cellular membranes in patients with ICUAW, causing skeletal muscle “intracellular glucose starvation” and a failure of AMP-activated protein kinase to respond to the impairment of ATP production. Most notably, in five subjects, these abnormalities were alleviated by NMES. In light of this, the relative increase of complex II capacity observed in our pilot study may represent a functional adaptation of muscle to the increased reliance on fatty acid oxidation. It is not known whether the severity of mitochondrial functional alteration reflects the degree of insulin resistance and the severity of muscle weakness, and whether the delivery of very early FES-CE has a potential to influence these changes.

In the light of this, we hypothesize the following:
H_1_: As most of the damage to the structure and function of skeletal muscle occurs during the first week, intensified goal-directed rehabilitation, which includes FES-CE and starts within 48 h after ICU admission, improves the functional outcome of ICU survivors at 6 months when compared to the standard of care.H_2_: The intervention, as compared to standard of care, shall preserve muscle mass and improve muscle power at ICU discharge.H_3_: The intervention, as compared to standard of care, shall increase insulin-mediated whole-body oxidative glucose disposal and mitochondrial functional indices.

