## Methods

### Enrolment and randomization

All patients admitted to participating ICUs are screened daily by research nurses and all eligible patients or their representatives are approached by investigators as soon as possible, but always within 72 h of admission. Participants for whom informed consent was obtained will be randomly assigned (1:1) to receive either standard care or the intervention using offsite independent randomization protocols (www.randomization.com) embedded in the electronic case report form. Randomization will be stratified according to the presence or absence of sepsis and the availability of a biopsy at baseline. There is no restriction (blocking) during randomization.

Both the study team and clinical personnel will be made aware of subject treatment allocation. The outcome assessor is not involved in patient care and remains blinded to treatment allocations.

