### Complementary studies: insulin resistance and mitochondrial function

These studies will be performed in addition to other study procedures in a nested subgroup of patients, who give specific consent. The first measurement will be performed at baseline prior to randomization, ideally the next morning after admission. Second measurement will be performed on day 7 of ICU stay, i.e. after at least 5 days of intervention.

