#### Muscle biopsy

Muscle biopsy will be performed from the vastus lateralis muscle using the Bergstrom needle biopsy technique. The sample will be separated into three parts (50–100 mg each). One part will be immediately frozen in liquid nitrogen for analysis of the protein/DNA ratio and for protein expression studies. The second part will be frozen in liquid nitrogen-cooled isopentone for muscle fibre typing and immunohistochemistry analysis. The third part put will be placed in BIOPS media on ice for the preparation of homogenates and measurement of citrate synthase activity, spectrophotometric analysis of the activity of respiratory complexes I–IV [52] and western blot analysis of respiratory complexes (as described in [55]). In the fresh muscle homogenates, we will use high-resolution respirometry (Oxygraph; Oroboros, Austria) to determine the function of individual respiratory complexes in the cytosolic context and measure basic functional metabolic indices by a method we have recently developed and calibrated against isolated mitochondria [59]. We will specifically look at the degree of mitochondrial uncoupling, the respiratory chain capacity and the function of individual complexes, including glycerol-3-phosphate shuttle. From the satellite cells we will prepare a culture of myotubes, which will serve as an in vitro model of skeletal muscle [60] and specifically measure the in vitro ability of myotubes to oxidize fatty acids by extracellular flux analysis (Seahorse Biosciences). Frozen muscle samples will be stored at − 80 °C for analysis of the DNA/protein ratio, mRNA and proteins involved in the regulation of proteolysis, substrate oxidation and anabolic pathways of skeletal muscle (MuRF, FOXO, atrogins) as well as immunohistochemistry and typing of muscle fibres. In order to determine which changes are caused by critical illness itself, we will also obtain control samples (*n* = 15) from age, sex and BMI-matched metabolically healthy volunteers undergoing elective hip surgery at the Department of Orthopaedic Surgery. In addition, we will look at the change of these indices after 7 days of critical illness and the influence of the intervention versus standard of care. We will look at correlation of these parameters with muscle power (i.e. compare the bioenergetics profile of skeletal muscle in those who develop ICUAW and in those who do not) and insulin resistance.

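### The planned association of mitochondrial indices with insulin resistance and with ICU-acquired weakness mixes both randomised arms with no account of arm stated, so a strong treatment effect could leak into it

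*Protocol article*

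**What the plan says.** The abstract sets the size of the subgroup: "In a subgroup (*n* = 30) we will assess insulin sensitivity and perform skeletal muscle biopsies". Under Enrolment and randomization, "Randomization will be stratified according to the presence or absence of sepsis and the availability of a biopsy at baseline", so the subgroup contains patients from both arms.

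The Muscle biopsy section then plans two different things with these patients' data.

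- An arm comparison: "the change of these indices after 7 days of critical illness and the influence of the intervention versus standard of care".
- An association: "We will look at correlation of these parameters with muscle power" and with insulin resistance. The muscle-power part is explained as an intention to "compare the bioenergetics profile of skeletal muscle in those who develop ICUAW and in those who do not". Arm is not mentioned here, nor is it stated whether baseline, day-7 or change values are used.

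The hypotheses at the end of the Rationale predict treatment effects on all the variables involved. H2 says the intervention "shall preserve muscle mass and improve muscle power at ICU discharge"; H3 says it "shall increase insulin-mediated whole-body oxidative glucose disposal and mitochondrial functional indices".

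On timing, the Complementary studies section says "The first measurement will be performed at baseline prior to randomization". The second biopsy and clamp follow on day 7, after at least five days of intervention.

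**The concern.** The Rationale lists two separate unknowns: whether mitochondrial alteration goes along with insulin resistance and weakness, and whether very early FES-CE changes these things. The association analysis addresses the first and the arm comparison the second.

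If the intervention improves both the mitochondrial indices and insulin sensitivity, the two arms form two clusters displaced in the same direction on both axes. A correlation across all 30 patients then picks up that displacement even if the two variables are unrelated within each arm. The same holds for the ICUAW contrast: if the intervention preserves muscle power, the patients without ICUAW include more intervention patients, and the contrast becomes partly the arm comparison under another label.

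What is at stake is the mechanistic reading. A pooled association after randomisation could be reported as evidence that mitochondrial function tracks weakness or insulin resistance when it shows only that both responded to treatment. The primary outcome and the listed secondary outcomes are not affected.

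**Working it through.** The article gives no figure for this analysis, so there is nothing to reproduce. The check asks how large the leakage could be.

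**Inputs from the article.** Subgroup of 30 (abstract); 1:1 allocation, with biopsy availability as a stratification factor (Enrolment and randomization).

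**Assumptions.** 15 patients per arm (from the 1:1 ratio; randomisation is unblocked, so the actual split may differ); no correlation within arms; arm shifts d1 and d2 in within-arm SD units, varied over a range because no effect size is given; a two-sided 5% test, used as a conventional yardstick.

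**Induced correlation.** With equal arms, a shift d adds d²/4 to a variable's total variance, and the two shifts together add d1·d2/4 to the covariance. Hence

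r = (d1·d2/4) / √[(1 + d1²/4)(1 + d2²/4)],

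which for equal shifts is r = (d²/4)/(1 + d²/4).

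- d = 0.5: 0.0625/1.0625 = 0.06
- d = 0.8: 0.16/1.16 = 0.14
- d = 1.06: 0.2809/1.2809 = 0.22
- d = 1.5: 0.5625/1.5625 = 0.36
- one variable shifted, the other not: the numerator is 0, so r = 0

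For comparison, the |r| needed for significance at n = 30 is 0.36. The value 1.06 SD is the arm difference that 15 per arm can detect with 80% power (two-sample t test, two-sided 5%). It marks where the subgroup could itself demonstrate an effect; it is not an expected effect.

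**Rejection rates.** Simulation with 40,000 runs per row. The pooled and adjusted columns test a Pearson correlation without and with centring by arm. The ICUAW column compares the index between patients with and without weakness, ignoring arm, on the further assumption that about half of the subgroup develops ICUAW.

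| Shift in both variables (SD) | Induced r | Pooled correlation | ICUAW contrast, arm ignored | Correlation adjusted for arm |
|---|---|---|---|---|
| 0 | 0 | 5% | 5% | 5% |
| 0.5 | 0.06 | 6% | 6% | 5% |
| 0.8 | 0.14 | 11% | 10% | 5% |
| 1.06 | 0.22 | 22% | 18% | 5% |
| 1.5 | 0.36 | 54% | 46% | 5% |

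If only one variable shifts, the pooled test rejects in 5% of runs. Adjusting the ICUAW contrast for arm also returns it to 5%.

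**Price of adjusting.** With no shift and a true within-arm correlation of 0.5, power is 82.7% pooled and 81.3% adjusted.

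**Baseline.** The first biopsy and clamp precede randomisation, so d1 = d2 = 0 by design and that correlation carries no treatment effect.

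**The case against.** The strongest reply is that the article never says the arms are pooled or that arm is ignored. It is a condensed text, and the covariates of an exploratory analysis in 30 patients are commonly left to a fuller plan. This stands in part: the point can only be that no account of arm is stated. It is not mere silence, however, because the text places the arm comparison first and then defines a separate grouping, by weakness, which on a plain reading cuts across arms.

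A reader might infer several stronger things that the documents do not support.

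- **That the plan breaches its own 5% error rate.** The level in the Data analysis plan is set for between-arm comparisons of the primary and secondary outcomes. This association is not among them, and no confirmatory test is promised.
- **That a false mechanistic finding follows whenever the intervention works.** Both variables must move, and by roughly 0.8 SD or more, before the inflation matters. At 0.5 SD it is about one percentage point.
- **That H3 alone creates the problem.** H3 covers the indices and glucose disposal. Muscle power comes from H2, which places the effect at ICU discharge, whereas the last biopsy is on day 7.
- **That the data cannot separate the two questions.** Arm is known for every patient, the arm effects on the indices and on glucose disposal are to be compared anyway, and the baseline measurements are free of treatment.

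It can also be said that if the intervention acts on strength or insulin sensitivity through mitochondria, the between-arm component is part of the mechanism and not an artefact. That is fair, but a pooled correlation cannot distinguish it from two independent responses to treatment. Reporting the arm effect and the within-arm association side by side loses neither.

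**Conclusion.** The concern holds as a minor point about an exploratory, post-randomisation analysis. As written, the association is planned in a subgroup containing both arms with no account of arm stated, and a strong effect of the intervention on both variables would inflate it. The inflation ranges from negligible (6% at 0.5 SD) through moderate (11% at 0.8 SD, 22% at 1.06 SD) to severe (54% at 1.5 SD). These figures rest on 15 per arm, no within-arm correlation and equal shifts, none of which the documents supply; the ICUAW figures rest in addition on half of the subgroup becoming weak. An analysis plan not shown here may already adjust for arm.

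**What to change.** Add a sentence stating that associations of the mitochondrial indices measured on day 7 or later with insulin resistance and muscle power, including the comparison of patients with and without ICUAW, are adjusted for treatment arm, by partial correlation or by a regression with an arm term. Name the time point used for each association. Report the correlation of the pre-randomisation indices with the pre-randomisation clamp values separately, as the estimate that treatment cannot influence. Plots with the arms marked would let readers see whether a relation is present within each arm.

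No new data are needed. The cost is one degree of freedom, which at n = 30 and a true correlation of 0.5 takes power from 82.7% to 81.3%.

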### Statistical analyses

#### Sample-size calculation

In studies of critical illness outcome at 6 months using SF-36 scores, the standard deviation varied between 10 and 30 points. In order to have 80% power to detect a 15-point difference in SF-36 scores between control and intervention at the level of significance *p* < 0.05 in the population with a mean of 60 and SD of 30 [12], we would need 108 subjects (54 in each arm). In order to allow for deaths and dropouts, we plan to randomize 150 subjects.

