#### Primary outcome

The primary outcome is the physical component of the SF-36 quality of life questionnaire measured in ICU survivors at 6 months. Based on the study by Kayambu et al. [12], where this measure was 60 ± 29 points in the control group, our study is powered to detect a change by 15 points or more, which is within the limits determined as clinically important for patients with COPD, asthma and myocardial infarction [56]. The SF-36 has been validated in the Czech Republic and endorsed by the Institution for Health Information and Statistics (https://www.uzis.cz/en/node/8159).

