#### Data analysis plan

The primary outcome and all secondary outcomes will be compared between the intervention and standard of care groups in an intention-to-treat population, with all tests two-sided and with the level of significance set at 5%, after the primary outcome has been collected in the last subject. There is no plan for any interim analysis. We will perform exploratory analyses in pre-specified subgroups of patients stratified according to APACHE II, and the length of intervention. We will also perform unadjusted analysis of odds ratio of being functionally independent (defined as ability to walk, use a telephone, self-care, use the toilet and groom) at 6 months after ICU admission in patients in the intervention and standard of care groups. We will perform adjustments on the disease severity (APACHE II score), admission diagnosis, baseline functional status and age. Missing data for primary outcome will be dealt by reporting both worst-case and per-protocol results; no imputation will be used.

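### With the plan's own inputs, 54 per arm gives 73% power rather than 80%, and 150 randomised tolerates about 15% loss rather than the implied 28%

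*Protocol article*

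**What the plan says.** The Sample-size calculation section sets the target as "80% power to detect a 15-point difference in SF-36 scores between control and intervention". It takes a 5% significance level and plans on an SD of 30 around a mean of 60. Its result is "we would need 108 subjects (54 in each arm"). On losses, the same section says: "In order to allow for deaths and dropouts, we plan to randomize 150 subjects". No attrition rate is given.

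Three other places bear on the calculation:

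- Data analysis plan: the comparison is made "with all tests two-sided and with the level of significance set at 5"%, and no interim analysis is planned.
- Enrolment and randomization: allocation is 1:1.
- Primary outcome: the outcome is the SF-36 physical component in ICU survivors at 6 months. The source figure is quoted as "where this measure was 60 ± 29 points in the control group", from the same cited study that supplies the SD of 30.

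**The concern.** Every input to a standard two-sample calculation is stated, so the sample size can be checked directly. The familiar result for a standardised difference of 0.5 (15/30) at two-sided 5% and 80% power is 63 to 64 per arm. The plan's 54 is well below that.

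Two things are at stake. First, the power claim for the only primary outcome would be untrue for the inputs given, and a reader of a null result would credit the trial with more sensitivity than it had. Second, 150 is justified as 108 plus a margin for losses. If 108 is too low, the margin is smaller than it looks. That matters for ventilated patients expected to stay at least 7 days in intensive care, whose outcome exists only if they survive 6 months, and for whom the Data analysis plan rules out imputation.

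**Working it through.** **Inputs.** Difference 15, SD 30, power 80% (Sample-size calculation); two-sided 5%, no interim analysis (Data analysis plan); 1:1 allocation (Enrolment and randomization). Variant SD 29 (Primary outcome).

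**Required number, normal approximation.** n per arm = 2 × (z₀.₉₇₅ + z₀.₈₀)² × (SD/difference)²

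= 2 × (1.960 + 0.842)² × (30/15)² = 62.8, so 63 per arm (126 in total).

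**Required number, t-test (noncentral t).** 63.8, so 64 per arm (128 in total).

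The stated 108 is not reproduced. The requirement is 126/108 = 1.17 to 128/108 = 1.19 times the stated number, which is too large a gap for rounding.

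**Attempts to recover 54 per arm**

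| Variant | n per arm for 80% power | Power at 54 per arm |
|---|---|---|
| SD 30, two-sided (as stated) | 63 (normal), 64 (t) | 73.8% (normal), 73.1% (t) |
| SD 29, two-sided | 59 (normal), 60 (t) | 76.7% (normal), 75.9% (t) |
| SD 30, one-sided | 50 (normal), 51 (t) | 83.0% (normal), 82.6% (t) |
| SD 29, one-sided | 47 | 85.1% (normal), 84.7% (t) |
| SD 30, two-sided rank test (64/0.955) | about 67 | not computed |

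None gives 54. Solving backwards for two-sided 5% and 80% power with 54 per arm:

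- SD, normal approximation: 15 / [√(2/54) × (1.960 + 0.842)] = 27.8. By t-test it is 27.6. The protocol gives neither value.
- Difference at SD 30, t-test: 16.3 points instead of 15.

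**Attrition margin within 150 randomised**

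- Implied by the stated requirement: 1 − 108/150 = 28.0%, or 42 patients.
- Needed to keep 80% power, t-test: 1 − 128/150 = 14.7%, or 22 patients.
- Needed to keep 80% power, normal approximation: 1 − 126/150 = 16.0%, or 24 patients.

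**Power by loss, SD 30, two-sided t-test.** The protocol gives no loss rate, so apart from the implied 28% the rates below are illustrative assumptions.

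| Loss | Evaluable | Power |
|---|---|---|
| 0% | 150 | 86.0% |
| 10% | 135 | 82.2% |
| 20% | 120 | 77.5% |
| 28% (implied) | 108 | 73.1% |
| 30% | 105 | 71.8% |
| 40% | 90 | 65.0% |

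**The case against.** The arithmetic itself is hard to contest; the fair objections concern its weight.

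- **The plan never states 28%.** True. It is only what 108 of 150 implies, and the tolerable figure depends on method (14.7% or 16.0%). The comparison stands on that footing.
- **SD 29 against SD 30 is harmless rounding.** Largely accepted. Rounding up is conservative, and 30 is also the top of the range the plan quotes ("the standard deviation varied between 10 and 30 points"). It is an editorial inconsistency about one cited figure, and neither value produces 54.
- **SD 30 is pessimistic.** At an SD of 25, inside the quoted range, 54 per arm would give 87% power and 45 per arm would still give 80%. This means the trial may turn out adequately powered. It does not make the stated number right for the SD the plan chose.
- **150 is not shown to be too few.** Agreed. At SD 30, power falls below 80% only when loss passes about 15%. The error lies in the stated requirement and the margin derived from it.
- **Covariate adjustment might explain 54.** It would need a covariate–outcome correlation of roughly 0.37 (normal) to 0.39 (t) at SD 30; at 0.3 the power with 54 per arm is 77%. The calculation mentions no adjustment and the protocol gives no such correlation. The Data analysis plan does list adjustment for APACHE II, admission diagnosis, baseline functional status and age, but it does so straight after the functional-independence odds ratio, so it is unclear whether this covers the primary outcome.

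**Conclusion.** The concern holds. For a 15-point difference, SD 30, two-sided 5% and 1:1 allocation, 54 per arm gives 73% power, about 7 percentage points below the claim. The requirement for 80% is 128 evaluable patients (126 by normal approximation), which is 20 (or 18) more than stated. The margin for deaths and dropouts within 150 is about 15%, roughly half of the implied 28%.

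This rests on an unadjusted comparison of two means with a common SD of 30, which is what the calculation describes. A smaller true SD, or prognostic covariates in the primary analysis, would improve the position; a loss above 15% at SD 30 takes power below 80%. The number randomised is not shown to be inadequate. The power statement for the primary outcome is wrong as written and should be corrected.

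**What to change.** Reword the Sample-size calculation section along these lines: *With SD 30, 64 per arm (128 evaluable) give 80% power to detect 15 points at two-sided 5%. Randomising 150 allows for about 15% loss to death or dropout. If 108 are evaluable, power is 73% and the difference detectable with 80% power is 16.3 points.* State the test assumed, and use one SD here and under Primary outcome, or say that 29 was rounded up to 30.

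Keep 150 as the number randomised. As a separate and optional choice, the Data analysis plan could make clear that its listed covariates apply to the primary outcome. That could recover some precision without more patients, but the protocol gives no basis for saying how much, so it should not be counted in the power statement.

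The cost is wording only. No patients or procedures are added, and the stated power becomes less favourable.
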